Systematic reviews have highlighted the need to better understand the mediators of knowledge transfer, and previous work has established that a variety of factors may influence the effects of KT [38,39]. However, the mediators are usually only addressed as secondary issues, and few high-quality studies or literature synthesis have been conducted. Prior knowledge, education, and age have been considered as demographic predictors. We will evaluate the role of these previously studied predictors. However, we also wish to identify unknown predictors. To fully address KT mediators, it is important to have an in-depth understanding of responses to knowledge transfer; this requires qualitative research that identifies and characterizes the elements that facilitate or obstruct KT. It is our belief that it is important to identify mediators that could be used to maximize KT effectiveness using a proactive approach. 'Readiness to Change,' also called the Transtheoretical Model, incorporates features of a variety of behavior models to describe the stages of change. It has been used in addiction, health promotion, organizational change, and professional practice literature, most commonly health behavior applications [40,41]. More recently, some have suggested that Readiness to Change may provide a greater depth of understanding of how participants respond to knowledge transfer [42]. Specifically, these investigators used a Readiness to Change questionnaire to evaluate how KT affected intent and action to a short course on knowledge transfer. The Readiness to Change model suggests that change in behavior is modulated by a person's readiness to make changes at the time the information is provided [40,41,43]. In other words, "*the right information and the right process – at the right time.*" The stages are: **Precontemplation **(uninformed about the need for change, uninterested in changing behavior), **Contemplation **(thinking about change in the near future), **Preparation **(ready to make a change in the next month), **Action **(implementing a specific action plan), and **Maintenance **(continuation of desirable actions). The model developers [44-46] and subsequent studies [40,43,47-51] suggest that categorizing people in stages allows one to customize messages and strategies specific to the participant's stage. This concept has not been applied to KT, but if we demonstrate that readiness to change mediates responses in this study, it will provide a promising approach to customize knowledge transfer to users. We will use the qualitative component of the study to understand the decisional balance inherent in the Transtheoretical Model.

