### Secondary objectives

1. To identify the key elements of SHIPS and e-PBL that engage participants in KT and assist them in addressing barriers to change;

2. To determine whether clinicians exhibit a decisional balance and spectrum of behaviors consistent with the Transtheoretical Model of (Readiness to) Change; and

3. To determine the relative importance of potential predictors of change, including characteristics of clinicians (years of practice, highest degree, Readiness To Change), practice settings (practice type, caseloads, years of experience), and how they affect knowledge acquisition and implementation following KT interventions.

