#### Group assignment procedure

A randomized design is usually the most rigorous, allowing for control of known and unknown confounders. In this case, it is not the most appropriate design strategy and we have selected a quasi-experimental approach. Research design methodologists have indicated that attaining an equal distribution of confounders in small samples via randomization, such as that required for the present study, is unreliable. Therefore we will use a non-randomized allocation procedure called minimization, which places participants in intervention groups to minimize the differences across key predictors [69-71]. We have identified pre-test scores, years of practice, practice area (urban/rural), and practice type (PT/OT) as the key predictors. Minimization across key predictors will balance prognostic variables and result in more valid comparisons [71]. Subjects will be allocated using minimization within orthopedic and pediatric groups at each site. At each site the pool of subjects will be allocated minimizing difference by: creating pair groupings based on professional training (PT/OT), matching area practice and then most similar pre-test scores, and, finally, by minimizing years of practice. We then will conduct descriptive analyses of group similarities and test whether we can optimize groups' consistency by reallocation of assignment. When this process is complete, subjects at each site will be informed of their assignment.

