## Analyses

### Quantitative analyses

All data will be double-entered in SPSS 14.0. Descriptive analyses will be conducted, including checking for outliers, normality testing, and univariate correlations. The first primary analysis (Objective 1) will be a two-way repeated measures analysis of variance to determine primary unadjusted differences in absolute scores over time, and between groups for each of the three primary outcome measures: knowledge, utilization, and chart-stimulated recall scores. An analysis of covariance will be used to compare these same effects adjusting for baseline knowledge score, Readiness to Change, years of practice, and educational preference. These analyses across the e-PBL and SHIPS groups will determine the relative effectiveness of these two alternative knowledge transfer choices. Effect sizes and their 95% confidence intervals will be calculated to determine whether there are differential impacts on change in knowledge, utilization, and integration of knowledge between the two different KT approaches. For the secondary research question (Objective 2.3) on the relative importance of KT predictors, a multiple linear regression [79,80] will be used to develop models of how years of practice, educational background, caseload characteristics, educational preferences, or Readiness to Change predict changes in knowledge, utilization, or integration following knowledge transfer interventions, with KT method as a covariate.

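### Secondary objective 3 names practice type as a predictor of change, but the regression assigned to that objective does not list it, so as written its relative importance is not estimated

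*Protocol article*

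**What the plan says.** The Protocol article, Secondary objectives (item 3), commits to the relative importance of two groups of predictors: "characteristics of clinicians (years of practice, highest degree, Readiness To Change), practice settings (practice type, caseloads, years of experience"). Practice type and caseloads are separate items in that list.

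The same article, Group assignment procedure, names four variables for minimization. Besides pre-test score and years of practice, it gives "practice area (urban/rural), and practice type (PT/OT) as the key predictors". This is the only place where practice type is defined.

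Quantitative analyses then ties one model to the objective by number: "For the secondary research question (Objective 2.3) on the relative importance of KT predictors, a multiple linear regression". That model is to show how "years of practice, educational background, caseload characteristics, educational preferences, or Readiness to Change predict changes in knowledge, utilization, or integration" are related, "following knowledge transfer interventions, with KT method as a covariate". Practice type is not in the list. It is also not among the ANCOVA covariates in the same section, which are baseline knowledge score, Readiness to Change, years of practice and educational preference.

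**The concern.** The objective asks which predictors matter more than others. A ranking from a regression covers only the variables that are in it. If practice type is left out, the trial cannot report from this model whether physical and occupational therapists responded differently, although the objective names practice type and the allocation treats it as key.

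A second, conditional matter concerns the remaining coefficients. Education, caseload and years of practice may differ between the two professions. If profession also affects change, those coefficients would carry part of its effect when it is omitted.

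**Working it through.** **1. The two lists side by side.**

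| Item in secondary objective 3 | Counterpart in the regression |
|---|---|
| Years of practice | Years of practice |
| Highest degree | Educational background |
| Readiness to Change | Readiness to Change |
| Practice type | None |
| Caseloads | Caseload characteristics |
| Years of experience | Years of practice |

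Five of the six items have a counterpart. Practice type does not.

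**2. The plan's sample size, used below.** With a standardized effect of 0.50, two-sided alpha of 0.05 and power of 0.80, a two-sample t-test needs 63.8, so 64 per group, as stated. The total is 2 × 64 = 128, and 128 / 0.9 = 142.2 (the plan prints 142 and rounds up to 144). The point does not depend on this figure; 128 completers serve only as the working sample size.

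**3. Cost of one more term.** Assume one parameter per predictor. The model as written has an intercept, KT method and five predictors, so 7 parameters and 128 − 7 = 121 residual degrees of freedom. With practice type it has 8 parameters and 128 − 8 = 120.

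**4. Size of possible confounding (assumed inputs, not in the documents).** Let profession shift the outcome by g (in residual SDs), let p be the share of one profession, and let ρ be the correlation of profession with another predictor that is standardized and has no true effect. If profession is omitted, the expected slope of that predictor is

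g × ρ × √(p(1 − p)).

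For g = 0.5, ρ = 0.4 and p = 0.5 this is 0.5 × 0.4 × 0.5 = 0.10. Simulation with n = 128 and 3,000 runs per setting, regressing the outcome on that predictor alone, gave:

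| p | g | ρ | Expected slope | Simulated slope | Rejection at 5% |
|---|---|---|---|---|---|
| 0.5 | 0.3 | 0 | 0.000 | −0.002 | 5.1% |
| 0.5 | 0.3 | 0.2 | 0.030 | 0.033 | 6.8% |
| 0.5 | 0.3 | 0.4 | 0.060 | 0.058 | 9.8% |
| 0.5 | 0.5 | 0 | 0.000 | 0.000 | 4.8% |
| 0.5 | 0.5 | 0.2 | 0.050 | 0.051 | 9.1% |
| 0.5 | 0.5 | 0.4 | 0.100 | 0.099 | 18.3% |
| 0.33 | 0.3 | 0 | 0.000 | 0.000 | 4.5% |
| 0.33 | 0.3 | 0.2 | 0.028 | 0.028 | 6.2% |
| 0.33 | 0.3 | 0.4 | 0.056 | 0.053 | 9.0% |
| 0.33 | 0.5 | 0 | 0.000 | −0.001 | 4.2% |
| 0.33 | 0.5 | 0.2 | 0.047 | 0.045 | 7.7% |
| 0.33 | 0.5 | 0.4 | 0.094 | 0.095 | 17.7% |

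At zero correlation nothing is confounded. Across the non-zero correlations tried, the rate is 6.2% to 18.3%.

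**5. Precision after the change.** A predictor correlated ρ with profession has its standard error multiplied by about 1/√(1 − ρ²) when profession enters. At ρ = 0.5 this is 1/√0.75 = 1.15, so a standard error near 1/√128 = 0.088 becomes about 0.10.

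**The case against.** The strongest reply is that the regression uses broad labels and that one of them may cover practice type. Group assignment procedure itself refers to PT/OT as professional training, which could fall under educational background. In the objective, practice type stands among practice settings rather than clinician characteristics, so it might mean setting or clinical area and fall under caseload characteristics. Coding of such terms is normally left to the analysis plan.

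Part of this stands: the objective does not define practice type, and PT/OT is carried over from the allocation section. The rest is strained. The objective lists highest degree and caseloads apart from practice type, so the regression terms that correspond to those two items do not naturally include a third. Even if profession were folded into educational background, its own importance could not be read off unless it had its own term. If setting was meant, that is not named in the regression either. Nor is this a detail held back for another document, since the article prints a predictor list that does not match its own objective.

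It is also fair to say that this is an exploratory model for a secondary objective and that the main comparison is little affected. Univariate correlations are planned too, but they are descriptive, their variables are not named, and they do not give relative importance in a joint model.

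Three stronger readings are tempting and not supported:

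- A reader might infer that the other predictors will absorb the profession effect. That needs both a real effect of profession on change and a correlation with the listed predictors, and the documents give neither.
- A reader might infer from the Background ("Prior knowledge, education, and age have been considered as demographic predictors. We will evaluate the role of these previously studied predictors") that age is wrongly missing. That sentence is not the objective; the objective does not list age, and the sentence does not promise age in this regression.
- A reader might object that educational preference was added. The objective's list is introduced as a set of examples, and the section on baseline measurement states why preference is collected.

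**Conclusion.** The mismatch holds. Run as written, the regression for secondary objective 3 returns no coefficient for practice type, so that part of the objective goes unanswered. This rests on reading practice type as PT/OT, the only definition given.

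Confounding of the other coefficients is possible but unquantified. The 6% to 18% range illustrates assumed effects no larger than the 0.50 on which the study was sized, with assumed correlations of 0.2 and 0.4; it is not a forecast. It concerns the predictor model only. The contrast between SHIPS and e-PBL is largely protected, because subjects are paired first on PT/OT. The point is a moderate one: worth correcting before analysis, with no bearing on the sample size or the primary conclusion.

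**What to change.** In Quantitative analyses, add practice type (PT/OT) as a term in each of the three regression models, for change in knowledge, utilization and integration, and state in secondary objective 3 that practice type means PT/OT. The variable is already known for every participant, because allocation uses it.

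The cost is a wording change, about one residual degree of freedom per model, and slightly wider intervals for predictors that are correlated with profession. Deleting practice type from the objective would also make the two lists agree, but it would give up a question that the trial can answer with data it already has.

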## Abstract

**Background:**

A substantial number of valid outcome measures have been developed to measure health in adult musculoskeletal and childhood disability. Regrettably, national initiatives have merely resulted in changes in attitude, while utilization remains unacceptably low. This study will compare the effectiveness and mediators of two different knowledge transfer (KT) interventions in terms of their impact on changing knowledge and behavior (utilization and clinical reasoning) related to health outcome measures.

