### Study measures

#### Baseline measurement of eligibility, status, and potential KT predictors

Participants will be pre-screened to ensure inclusion criteria. Eligible participants will then complete a baseline knowledge pre-test (to avoid ceiling effects/lack of responsiveness). Participants also will complete a baseline information questionnaire to collect demographic data, practice patterns, and educational background. Survey measures of knowledge and behavior will be administered. This data collection also will include a measurement of the therapist's intent to use outcome measures, their general level of research utilization, and their readiness to change. This scale evaluating Readiness to Change [40,41,73] was developed to reflect the core elements of the five stages of change, but was specifically applied to changing clinical practice. Although all participants will have agreed to allocation during informed consent, they will be asked their preference with respect to e-PBL and SHIPS so that post-hoc analyses can determine the importance of educational preference as a mediator of response.

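### The predictor regression gives educational preference one slope for both arms and, separately, lists no baseline score

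*Protocol article*

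**What the plan says.** The Quantitative analyses section assigns a multiple linear regression to Objective 2.3. Its predictors are experience, education, caseload, preferred mode of learning and readiness, and the models are to show how these "predict changes in knowledge, utilization, or integration following knowledge transfer interventions, with KT method as a covariate". No product term with KT method is stated, and no baseline score is among the predictors.

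The same section's analysis of covariance for Objective 1 compares the arms "adjusting for baseline knowledge score, Readiness to Change, years of practice, and educational preference". Preference and readiness enter there as adjusters only, but baseline knowledge is included.

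The aims that bear on these models are stated in four places:

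- Secondary objectives, item 3: "To determine the relative importance of potential predictors of change".
- Study measures, baseline measurement: preference between e-PBL and SHIPS is asked "so that post-hoc analyses can determine the importance of educational preference as a mediator of response".
- Background: "if we demonstrate that readiness to change mediates responses in this study, it will provide a promising approach to customize knowledge transfer". The Background also counts prior knowledge among the already-studied predictors and commits to evaluating it.
- Abstract: the study will "compare the effectiveness and mediators of two different knowledge transfer (KT) interventions".

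**The concern.** Preference between SHIPS and e-PBL differs in kind from years of practice. A wish for face-to-face teaching should help someone placed in SHIPS and may hinder someone placed in e-PBL. Its importance to response is therefore mainly a preference-by-method question, and neither specified model contains that term. The study could report that preference is unimportant when it in fact decides which mode suits whom.

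The second worry concerns the objective that the regression does serve. Change is the follow-up score minus the baseline score, so participants who start low tend to gain more and those who start high tend to gain less. Without baseline in the model, any predictor related to the starting score picks up part of that pattern, and the ranking of predictors is distorted.

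The word mediator adds to the confusion. A preference recorded before allocation cannot lie on the path from assigned mode to outcome. It can only predict or moderate.

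**Working it through.** **Plan's own figure.** Inputs from Sample size requirements: two-sided alpha 0.05, effect size 0.50, and 0.80, printed as Type II error but evidently the power (read literally it would give 11 per group). The two-sample t-test gives 63.8, so 64 per group and 128 in total; 128/0.9 = 142.2. The plan's 64, 128 and 142 reproduce, and are rounded up to 144. They cover the main contrast between arms only.

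**What one common slope does to a matching effect.** Let being in the preferred mode be worth m SD, and compare those who prefer SHIPS with those who prefer e-PBL.

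- Preference effect within SHIPS: +m. Within e-PBL: −m.
- Common slope with equal arms: (m − m)/2 = 0.
- Interaction: m − (−m) = 2m. With m = 0.5 SD the interaction is 1.0 SD and the additive coefficient is 0.
- If preference matters in one arm only (+0.5 and 0), the common slope is 0.25 and the interaction 0.5. The effect is then diluted, not lost.

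**Precision of the interaction.** The documents give no inputs for this. Assume SD 1, a binary preference with share p, and equal arms within each preference group.

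SE = sqrt(4/(Np) + 4/(N(1−p))); power at 0.5 SD = Φ(0.5/SE − 1.96); detectable with 80% power = 2.80 × SE.

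For N = 128:

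| p | SE | power at 0.5 SD | detectable (80%) |
|---|---|---|---|
| 0.5 | 0.354 | 29% | 0.99 SD |
| 0.3 | 0.386 | 25% | 1.08 SD |
| 0.2 | 0.442 | 20% | 1.24 SD |

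With all 144 analysed, power is 32%, 28% and 22%. About 503 completers would be needed for 80% power at 0.5 SD with p = 0.5.

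**Baseline, checked separately.** Assume unit-variance scores, a baseline-to-follow-up correlation of 0.5, and a standardized continuous predictor with correlation ρ to baseline and no true effect. Regressing change on the predictor without baseline has expected slope (0.5 − 1) × ρ, which is −0.15 at ρ = 0.3 and −0.25 at ρ = 0.5. In 4,000 simulated trials of 128, the null predictor was declared significant in 39% and 81% of runs. With baseline in the model the rate was about 5%. At ρ = 0 there is no bias.

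**Are the two gaps linked?** The simulation was repeated with a true slope difference between arms of 0.5 per SD of the predictor and no average effect. At ρ = 0 the additive model flagged the predictor in 5.1% of runs, its false-positive rate. The interaction model recovered 0.50 with baseline (power 87% to 89%) and without it (79% to 81%). Omitting baseline costs some precision for the interaction but does not hide it. These powers exceed those in the table because 0.5 per SD of a continuous predictor is a larger effect than 0.5 between two groups.

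**The case against.** Objective 2.3 asks who changes more after knowledge transfer, allowing for method. It does not ask who does better in one mode than the other, and a main-effects regression is a recognised answer. That stands: the missing interaction conflicts with the reason given for collecting preference, not with Objective 2.3.

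The baseline measurement section also foresees post-hoc analyses of preference, and a condensed article may leave their terms to a fuller document. A reader might infer that the study has no means of examining preference match; the article does not support that. What remains is that both models it does specify use preference additively.

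A reader might also infer that readiness needs the same term. The Background speaks of fitting messages and strategies to a participant's stage. It never proposes choosing SHIPS or e-PBL by stage, so a main effect of readiness can address the stated interest.

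The relation between predictors and starting score is not documented, so the 39% and 81% illustrate and do not forecast. The section also speaks of developing models, so its list may not be final. Both remarks are fair, but the Background's commitment on prior knowledge is still not carried into the list.

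Finally, an interaction this imprecise will usually be inconclusive. That is a reason to label it exploratory and show its interval, not to use a model that cannot express it.

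**Conclusion.** The concern holds as two independent points of modest weight.

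1. As specified, preference has one slope for both arms. A symmetric matching effect of any size would average to zero, and a one-sided effect would be halved. The trial can detect only a large interaction, about 1.0 to 1.2 SD with 80% power at 128 completers. This rests on SD 1, a binary preference with a 20:80 to 50:50 split, and equal arms within preference groups.
2. Change is modelled with no baseline score listed. The bias in predictor effects is −0.15 to −0.25 SD per SD of predictor under the assumed correlations, and zero if predictor and starting score are unrelated.

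It is tempting to join these and say that leaving out baseline is why differential response cannot be seen. That is wrong: only the missing interaction has that consequence. Nor is Objective 2.3 beyond reach, since a main-effects model can address it once baseline is included.

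**What to change.** - Add a preference-by-KT-method term to the regression, or state it for the foreseen post-hoc preference analysis. Report the estimate with its 95% confidence interval, labelled exploratory. A readiness-by-method term is optional.
- Include the baseline knowledge score as a covariate in the predictor regression. For utilization and chart-stimulated recall, include the baseline value where one is collected; the Study measures section does not clearly describe a baseline chart audit or recall.
- Call preference and baseline readiness moderators or predictors. Keep mediation for a variable measured after the intervention begins, such as readiness re-administered immediately afterwards.

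The cost is one interaction term, one baseline covariate per outcome model and some wording. Preference and baseline knowledge are already collected. The drawback is a wide interval for the interaction, which should not be read as evidence of no effect.
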